#### Multiple outcome testing

The study has a single primary outcome, as presented above. That will be the main result reported for the study and will not be adjusted for tests on secondary outcomes. We have secondary outcomes: (i) one on crime and (ii) two on co-offending. The study will adjust the co-offending analysis using the false-discovery rate [30]. All other analyses will be unadjusted. We know, *a priori*, that the study is not powered for sub-group analyses—any such analyses (along with anything not pre-specified) will be clearly labelled as exploratory.

#### Blinding during analysis

While the team are independently appointed evaluators, we will conduct analyses using masked treatment groups, so the analyst conducting the analysis will be blind to allocation.

### Formative process evaluation

The formative process evaluation will use a realist approach to explain how the study worked, in what context and with what population groups. It will address nine formative research questions:

To what extent were the three components of the intervention, as required by the YEF framework, received by the treatment population groups?How did inputs contribute to the intervention functioning?Who did the intervention work for, and how?How did local context affect intervention delivery?To what extent was the intervention delivered as intended?How did complexity affect intervention delivery?How did proximal outcomes change?Why did proximal outcomes change?What was learned from how the intervention was delivered?

The formative evaluation uses a mixed methods design, including qualitative, semi-structured cross-sectional and longitudinal interviews, and written researcher notes following the observations of regular meetings between the programme delivery team and programme participants. In addition, it uses quantitative, routine outcome performance monitoring deriving from administrative data. This includes a standardised set of criteria that the sites will collect as a part of the intervention and consists of, for example, the length of time needed for the participant to consent to being in the programme; the number of participants per delivery team member (community navigator/mentor); the number of meetings per participant; the length of being in the programme; the number of referrals to support services; and the number of referrals for enforcement. Sampling for interviews and observations varies, with researchers aiming for more individuals included in the first round of cross-sectional interviews and retaining as many as possible for repeat, longitudinal interviews and observations. Both interview and observation participants will be recruited with support from the delivery team, to reduce the possibility that participating in the study would discourage them from continuing the programme (e.g., out of fear that evaluators work with the police).

In this setting, high-quality logic models and context-mechanism-outcome (C-M-O) configurations are important to ensure the evaluability of the intervention. As shown in Table 3, these initial high-level C-M-O configurations will be used to test and develop a range of realist causal explanations that can be attributed to local ‘observable’ contexts. As an external expert ([name], London School of Hygiene and Tropical Medicine, UK) recommended, the evaluation contains limited C-M-O configurations centred on generally accepted ‘big’ ideas relevant to focused deterrence. Those have been previously used in the literature to plausibly explain why targeted deterrence, the provision of support, and community voice and legitimacy may affect specific individuals in varied contexts. During the early implementation phase, a final list of C-M-O configurations will be compiled for evaluation during the full implementation phase. The final list of conditions, aligned to the YEF implementation framework, will likely depend on the availability of relevant data, resources and the viability of testing configurations.

**Table 3 pone.0301023.t003:** Initial high-level C-M-O configurations (v2.0).

Context +	Mechanism =	Proximal outcome(s)
Heterogeneity in local resource availability and deterrence activities	[Targeted enforcement] An increase in legitimate targeted deterrence activities affects perceptions of certainty of arrest and punishment	Normative and instrumental non-violent modifications and engagement with individualised support
Variance in resource allocation, coordination, engagement, collaborations and spectrum of available support services	[Individualised support] Increase in availability of improved individualised support packages provides pathways to desistance and increasing perceptions of benefits	Sustained engagement with pathways to desistance and reorientation towards legal and social norms
Decrease in levels of community confidence in local policing and statutory and non-statutory support services	[Community validation] Social amplification of community moral voice, characterised by peer and familial influences, informal social controls, collective efficacy, and communicating shared values and beliefs, affects normative compliance and behaviour modification	Increase in legitimacy and support for intervention and enforcement activities to achieve normative compliance

The formative evaluation mainly focusses on targeted deterrence, individualised support, community validation and the interactions between these mechanisms, and the summative outcomes focus on violent offending and involvement in group violence.

### Data collection

The schedule for gathering data began in May 2023 and will run for at least two years. Various methods will be used to gather cross-sectional, longitudinal, and pre-post data from a variety of corroborative data sources. Data from the formative component will be thematically analysed to gain a shared understanding of how, why, and for whom the intervention worked in varied local contexts. The ability to delve deeply into the longitudinal qualitative data collected is a key advantage of the protocol design. Data collection methods include:

#### Semi-structured interviews

The experiences of programme participants, the delivery team, and stakeholders will be the focus of interviews. Due to the expected high dropout rates among programme participants, we will use convenience sampling and not limit the number of participants. We will offer vouchers equal to the UK living wage (~£15/h) as incentives to retain participants until the end of the intervention.

#### Observations

A standard observation protocol will be used to monitor participant and delivery team interactions, which will be influenced by the nine YEF FD framework criteria and each location’s unique intervention design. Researchers will document regular activities using structured and unstructured methods, noting discussion topics such as group dynamics, decision-making, available resources, and cultural contexts.

#### Administrative data

The delivery teams are responsible for gathering a wide range of intervention delivery and outcomes data. These data will help characterise the cohort, evaluate the balance between the intervention and control groups, outline participants’ journeys through the intervention, measure the degree of engagement, and detail when dropouts and completions occur. This information will be transferred to the evaluation team at regular intervals.

## Discussion

This protocol outlines the process and impact evaluation methodology for the most extensive multisite evaluation of focused deterrence in the UK. Spanning five distinct sites with seven trials, the evaluation includes a cohort of approximately 2,000 individuals, marking it as the only multisite trial of focused deterrence. The protocol uses an integrated realist evaluation framework with a multi-site parallel RCT design to evaluate the efficacy of focused deterrence as an intervention for reducing violent offending among individuals aged 14 and older who are at risk of violent offending in England. To the authors’ knowledge, this will be the first multi-site impact and process evaluation of a UK-based violence reduction intervention. The anticipated findings will offer pivotal insights for formulating future violence prevention policies in the UK. They are also expected to contribute significantly to the corpus of literature on violence prevention and intervention evaluation.

### Interim analysis and ‘backfire’ check

To mitigate the risk of iatrogenic effects, interim outcome analyses will be conducted roughly six months after the trial start date, defined as the date of first randomisation in any site. These analyses will aim to identify any adverse effects and/or clear evidence of harm, given the offending seriousness of the cohort involved, focusing on the direction and magnitude of the effects. However, it will not involve statistical analysis to avoid ‘alpha spending’ [31]. In the context of this intervention, harm is defined as a negative impact on offending (averaged across sites) where the reoffending prevalence in the treatment group is equal to or more than 10 percentage points greater than the control group prevalence (e.g., 20% in treatment, 10% in control).

Likewise, to act upon the potential risk of harm, we established a set of pre-specified limits or stopping rules that will inform the decision on the study continuation post the initial six-month period. These stopping rules allow for site-specific differences and avoid terminating the intervention in all sites if one site shows harmful effects during the interim analyses. The rules are:

if the average impact is negative, the study will pause intake for one month to allow for a discussion of options and agreement on study progressionif the average impact is positive, the threshold for roll-out to all participants will increase. To err on the side of caution, in this case, the reoffending prevalence would need to be 15 percentage points lower in the treatment group than control rather than 10 (e.g., 30% in control, 15% in treatment).

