## Summative impact evaluation

The summative impact evaluation has three research questions that will be examined during the 12-month follow-up period per participant. For evaluation purposes, the start of the intervention is operationalised as the point of randomization. The end is set as either the graduation from the programme (i.e., the point at which the delivery team and the programme participant jointly agree that the individual is no longer benefitting from the programme) or as dropping out from the programme due to, for example, imprisonment or death. Since it is unlikely that each individual will become a part of the programme immediately after being randomized into the treatment group, time from randomization to first contact by the delivery team is recorded in the process data and will be accounted for in the analysis.

The summative impact evaluation questions are as follows:

What is the difference in the number of violence against the person offences attributed to individuals receiving the focused deterrence intervention compared to those of similar individuals receiving business-as-usual support?What is the difference in the time to a violence against the person offence (in days) attributed to individuals receiving the intervention compared to those of similar individuals receiving business-as-usual support?What is the difference in the number of co-offending crimes (i.e., crimes involving two or more perpetrators) attributed to individuals receiving the intervention compared to those of similar individuals receiving business-as-usual support?

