### Randomisation

Eligible individuals within each site are randomised to treatment or control conditions on a 1:1 allocation ratio. Randomisation is stratified on (i) a three-point ordinal scale of frequency of offending in the past 24 months (derived from raw counts for each location but coarsened for randomisation to low, medium and high) and (ii) whether eligible participants are 18 years old and over or under 18 years of age. Stratification helps to reduce between-group differences at baseline, helping to increase statistical power with a fixed sample size [21].

Prior offending categories (tertiles) have been established from the first cohort of eligible individuals and are site-specific (i.e., grouping into low, medium and high might differ between sites). This method was chosen because it is transferrable across jurisdictions, easily accessible to analysts, and the data-generating process is relatively consistent across areas.

Our second stratification is whether a case is an adult (18 and over) or a child (under 18 years) since all sites expect a mix of such cases (noting that the minimum age is 14 years). This is necessary because statutory services in England generally treat children and adults differently, with deterrence and support provisions varying by child/adult status.

The evaluation team undertook the initial randomisation of long-listed eligible candidates as ‘batches’. Further randomisation will be undertaken on a case-by-case basis, as per a ‘trickle trial’ [22], using a dedicated randomisation platform that will record the individual’s unique ID, the site, their tertile of offending frequency, whether they are a child (under 18) at the time of randomisation, and treatment allocation. Records of treatment allocation are accessible to the trial’s delivery team and the evaluation team for data retention (trial duration plus 10 years). Random allocation of cases will be completed using the ‘randomizr’ package [23] for R v4.0.4 [24]. The sample code is recreated and available on the Open Science Framework: https://osf.io/pvnj2/.

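### The only described harm check applies a fixed 10-point prevalence margin, with no stated window or minimum follow-up, to at most about six months of unequal follow-up, and its harm definition and pause rule do not state the same trigger

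*Protocol article*

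**What the plan says.** All of the rule is in the protocol article, section on the interim analysis and backfire check.

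- **Timing.** "interim outcome analyses will be conducted roughly six months after the trial start date, defined as the date of first randomisation in any site". No other look is described.
- **Harm.** "harm is defined as a negative impact on offending (averaged across sites") in which "reoffending prevalence in the treatment group is equal to or more than 10 percentage points greater than the control group prevalence". The example given is 20% in treatment against 10% in control. The period over which prevalence is counted is not stated, nor is a minimum follow-up or number of participants.
- **Method.** Direction and magnitude only; "it will not involve statistical analysis to avoid" alpha spending.
- **Action.** "if the average impact is negative, the study will pause intake for one month", for discussion and agreement on how to proceed. The 10-point margin is not repeated in this rule.

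Three other places bear on it. Under Outcome measures, the primary outcome is counted over one year from randomisation. Under Randomisation, long-listed candidates were first randomised in batches, after which "Further randomisation will be undertaken on a case-by-case basis". Under Summative impact evaluation, "it is unlikely that each individual will become a part of the programme immediately after being randomized into the treatment group".

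**The concern.** The clock for the check belongs to the trial, while prevalence accrues on each participant's own clock. Six months after the first randomisation, the earliest entrants have about six months of follow-up and the latest have almost none. Cumulative prevalence rises with time at risk, so a harm that amounts to 10 points over 12 months shows as a smaller gap at the check. Any delay between randomisation and first contact shortens the exposed part of the window further.

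The section offers this check as the mitigation of iatrogenic effects in a cohort that includes children from age 14, and its result informs continuation. If the margin and the follow-up do not match, a result below the margin says little about harm over the outcome window. If the definition and the pause rule are different triggers, those applying them cannot tell from the text which one governs.

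**Working it through.** **What can be reproduced.** The example agrees with the margin: 20% − 10% = 10 points. The check has no stated sample size, base rate, horizon or operating characteristics, so there is no further figure to reproduce.

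**Inputs from the document.** One look at T = 6 months; margin 0.10; 1:1 allocation; batched, then case-by-case entry; 12-month outcome window.

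**Assumptions (not in the document).** Constant hazard of a first reoffence; exposure from randomisation; no recording delay; 12-month prevalences as listed; n = 100 or 200 per arm at the check; arms compared on pooled data. Three entry patterns are used: uniform over the six months, half on day 1 and half uniform, and everyone on day 1.

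**Formulas.** For 12-month prevalence p, the monthly hazard is h = −ln(1 − p)/12.

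- Everyone on day 1: prevalence at the check = 1 − exp(−6h).
- Uniform entry: average prevalence = 1 − [1 − exp(−6h)]/(6h).
- Half batched: the mean of these two.
- P(flag) = the exact two-binomial probability that the observed gap is at least 0.10.

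**Worked case, 20% v 30% at 12 months.** h = 0.0186 and 0.0297 per month. Uniform entry gives 5.4% v 8.4%, a gap of 3.0 points. Everyone on day 1 gives 10.6% v 16.3%, a gap of 5.8 points before rounding.

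**Reading 1: the margin refers to 12-month prevalence**

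| 12-month prevalence | Entry | Expected gap at check (points) | P(flag), n = 100 | P(flag), n = 200 |
|---|---|---|---|---|
| 10% v 20% | uniform | 2.8 | 0.9% | 0.03% |
| | half batched | 4.1 | 5.4% | 0.9% |
| | all day 1 | 5.4 | 14.0% | 5.4% |
| 20% v 30% | uniform | 3.0 | 3.6% | 0.4% |
| | half batched | 4.4 | 12% | 3.9% |
| | all day 1 | 5.8 | 22% | 12% |
| 50% v 60% | uniform | 4.3 | 17% | 7.5% |
| | half batched | 5.9 | 28% | 19% |
| | all day 1 | 7.5 | 38% | 31% |
| 40% v 60% | uniform | 8.0 | 39% | 32% |
| | half batched | 11.1 | 61% | 63% |
| | all day 1 | 14.2 | 77% | 84% |

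In every 10-point row the expected gap lies below the margin, so a larger sample makes a flag less likely. With 20% control prevalence at 12 months, treated prevalence would have to reach about 50% (uniform), 42% (half batched) or 37% (all day 1) before the expected gap is 10 points.

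**Reading 2: the margin refers to prevalence at the check.** A true 10% v 20% at that time is flagged 54% of the time at n = 100 and 53% at n = 200. Even with everyone on day 1, it corresponds to 1 − 0.9² = 19% v 1 − 0.8² = 36% at 12 months, a 17-point harm. Staggered entry makes the corresponding 12-month harm larger.

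**The pause rule read literally (any treated excess).** In the 20% v 30% case with uniform entry it fires 76% of the time at n = 100 and 87% at n = 200. With no effect and 10% prevalence in both arms at the check, it fires 45% and 47% of the time; over 50 to 400 per arm the range is 43–48%.

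**The case against.** A reader might infer that the check would almost never flag the harm it is meant to catch. The document does not support that, for four reasons.

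1. **Horizon.** The section does not say that the margin is a 12-month quantity. The definition and its example stand inside the interim check, and read there a true 10-point gap is flagged about half the time.
2. **Entry.** The first participants were randomised in batches, so wholly uniform entry is the unfavourable case. No site start dates are given, so how far some sites lag is unknown.
3. **Base rate and size of harm.** The section speaks of reoffending, not only violence, and Nottingham's criteria require a recent arrest, so high prevalence is plausible. At 40% v 60%, half batched, a flag is more likely than not.
4. **Pause rule.** Read literally it has no margin and is far more sensitive.

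It is also fair that an early calendar-timed look is a defensible choice for a harm check, and that numbers per arm and estimation detail commonly sit in a fuller protocol or analysis plan.

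These points rule out any single flag probability. They do not remove the mismatch, because the article itself fixes the clock and the margin. Nor does the pause rule settle matters: if it borrows the 10-point definition, the dilution applies to it too; if it has no threshold, it fires nearly half the time when there is no effect.

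**Conclusion.** The point holds in a conditional form. A fixed absolute margin is tied to a trial-level date, with no prevalence window or minimum follow-up. If the margin is a 12-month quantity, the check would usually miss a 10-point harm. With 100 to 200 per arm the flag probability runs from about 0.4% to 22% at 20% v 30%, depending on entry, and from about 8% to 38% at 50% v 60%. If it is a quantity at the check, a gap at the margin is flagged about half the time and stands for a 12-month harm of 17 points or more in the 10% v 20% example. Larger 12-month harms may be flagged more often than not.

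Separately, the harm definition and the pause rule do not state the same trigger and must be reconciled.

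The probabilities rest on the assumed hazard, base rates, entry patterns and numbers per arm; none is in the document. Delay to contact or in recording would lower the flag probabilities. The sponsor should act on this.

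**What to change.** Keep the early look and change four things around it.

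1. Compare arms by Kaplan-Meier cumulative prevalence at a stated common time from randomisation, using the offence dates already drawn from Police National Computer records.
2. State the horizon to which the margin refers, and the 12-month harm that the look can and cannot detect under stated base rates, entry pattern and numbers per arm.
3. Repeat the same descriptive harm comparison once, later, as follow-up matures.
4. Reconcile the harm definition with the pause rule, so that the text states one trigger or says what each is for, and report how often it would fire with and without harm.

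The size of the margin and the action taken are for the trial's oversight group. A common time horizon does not make the check sharp: a true gap exactly at the margin is still flagged only about half the time (54% at 100 per arm and 53% at 200 for 10% v 20%). That should be stated too.

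The cost is protocol wording and one extra descriptive run on data already being collected. The early look is not delayed.

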In the equation, *Y* is the outcome—in this case, a count variable measuring the number of violent offences attributed to an individual in the twelve calendar months following the randomisation of an individual. The analysis approach will be based on count outcomes. We intend to use a *zero-inflated Poisson* (as reflected in our power simulations) because many individuals will likely not have further offences in the follow-up period of 12 months post-randomisation. 1[treatment] will be a binary variable where 0 = control and 1 = treatment, and the coefficient from this variable in the model will be the focal result for the project. 2[offending frequency] is one variable used for stratification in each site. We acknowledge that there is a difference between the model used in the power calculation and the analysis model presented here (S1 File). We will update the power calculations for our statistical analysis plan once we have sample data from sites to understand the likely outcome distribution (based on pre-intervention outcome data). This will be included in the analysis as n-1 dummy categories, with the reference category being the category with the largest number of observations from low, medium, or high offending frequency (note that not pre-specifying which category now will not affect the results). 3[adult] will be a binary variable for whether an individual is an adult (over 18) (= 1) or a child (under 18 years of age) (= 0). 4[site] will be site fixed effects—dummy variables for n-1 sites, again with the site with the largest number of observations overall as the reference category (anticipated to be either Coventry or Wolverhampton in the West Midlands). We include this variable because we know, *a priori*, that sites will differ in their eligibility criteria and selection processes. Hence, we need to account for between-site variation in our analysis. Finally, 5[year/month] will be a variable that captures the year and month since the start of the delivery period. This measure will capture seasonal variation and any esoteric shocks during delivery. This will be entered as a continuous variable, but if there are model convergence problems, we will aggregate this to year-quarter. We also acknowledge that it may be necessary to include another variable for offender sex, depending on the number of females included. If necessary, this would be a binary variable with 0 = male and 1 = female, determined by sex at birth, if possible, to determine this from available data.

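### The interim pause rule omits the 10-point harm threshold defined just before it, and nothing printed acts on harm at a single site

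*Protocol article*

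**What the plan says.** All the rules are in the Protocol article, section Interim analysis and ‘backfire’ check. The check takes place about six months after the first randomisation in any site. It looks at direction and magnitude and excludes statistical analysis.

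- **Definition of harm.** Harm is an adverse effect on the cross-site average, and it is present "where the reoffending prevalence in the treatment group is equal to or more than 10 percentage points greater than the control group prevalence". The worked example is 20% against 10%.
- **Harm rule.** "if the average impact is negative, the study will pause intake for one month", so that options can be discussed and progression agreed. No size is given.
- **Benefit rule.** If the average impact is positive, the bar for rolling out to everyone rises: "the reoffending prevalence would need to be 15 percentage points lower in the treatment group than control rather than 10". A size is given.
- **Claim about sites.** "These stopping rules allow for site-specific differences and avoid terminating the intervention in all sites if one site shows harmful effects".

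Two other sections bear on the site question. Under Randomisation, "Eligible individuals within each site are randomised to treatment or control conditions on a 1:1 allocation ratio", and the randomisation platform records site and allocation for each person. Under Intention to treat analysis, the authors expect that "sites will differ in their eligibility criteria and selection processes".

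**The concern.** The definition and the rule are meant to work as a pair: one says what counts as harm, the other says what happens when it is seen. As printed, either the rule lacks its threshold or the threshold triggers nothing. Because the interim excludes statistical analysis, no test result can settle which reading applies when the data arrive.

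The two readings behave very differently. A direction-only rule responds to any adverse difference, however small, so under no true effect it fires about as often as a coin toss. A 10-point rule seldom fires by chance but misses more real harm. Those running the trial should know in advance which one they have, particularly as it enrols children from age 14.

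The second part concerns sites. The text says that the rules allow for site differences, but the harm definition and both rules refer to the average and the pause applies to the whole study. Nothing printed detects a harmful site or responds to it.

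**Working it through.** **No figure to reproduce.** The protocol gives no operating characteristics for these rules. Its two worked examples agree with their thresholds: 20% − 10% = 10 points, and 30% − 15% = 15 points.

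**Inputs.** From the document: 1:1 allocation and the 10-point harm threshold. Assumed, because the document does not state them: n = 50, 100, 200 or 400 per arm followed up at the interim, and control prevalence p = 10%, 20% or 30% (the span of the document's examples).

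**Formulae.** Let X_T ~ Bin(n, p + δ) and X_C ~ Bin(n, p), independent. The probabilities are summed exactly over all pairs of counts.
- Literal rule: P(pause) = P(X_T − X_C > 0).
- 10-point rule: P(pause) = P(X_T − X_C ≥ 0.10n).

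**No true effect (δ = 0).** By symmetry the literal rule fires with probability (1 − P(tie))/2. For n = 50 and p = 10%, P(tie) = 0.134, so (1 − 0.134)/2 = 0.433.

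| n per arm | p | Literal rule | 10-point rule |
|---|---|---|---|
| 50 | 10% | 0.433 | 0.066 |
| 50 | 30% | 0.457 | 0.163 |
| 100 | 20% | 0.465 | 0.046 |
| 200 | 20% | 0.475 | 0.007 |
| 400 | 10% | 0.477 | <0.0001 |
| 400 | 30% | 0.485 | 0.001 |

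Across all twelve combinations the literal rule pauses 43% to 48% of trials and the 10-point rule 0% to 16%. The first range hardly depends on the assumptions, since only the chance of a tie keeps it below one half.

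**True average excess of exactly 10 points (δ = 0.10).** The literal rule pauses in 83% (n = 50, p = 30%) to 100% (n = 400) of trials. The 10-point rule pauses in 52% to 55%, because the true value sits on the limit.

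**One harmful site (illustration).** Suppose one site is 30 points worse under treatment, the others show no effect, and the average is weighted by participants. If that site holds a share w of participants, the true average excess is 30w points. The chance that the 10-point rule fires, over the same n and p, is:

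| w | True average excess | P(pause), 10-point rule |
|---|---|---|
| 0.1 | 30 × 0.1 = 3 points | 0% to 26% |
| 0.2 | 30 × 0.2 = 6 points | 5% to 37% |
| 0.3 | 30 × 0.3 = 9 points | 36% to 50% |
| 0.4 | 30 × 0.4 = 12 points | 63% to 81% |

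Serious harm at one site is therefore usually diluted below the limit unless that site is large. The 30 points and the shares are assumptions that show the mechanism; they do not describe this trial.

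**The case against.** **The rule may be shorthand.** The definition speaks of a negative impact averaged across sites, and the rule reuses those words in the next paragraph. The benefit rule's change to 15 from 10 presupposes 10 as the default. A reader might infer from the literal text that the trial really will pause on any adverse difference, so that nearly half of null trials would be halted. The document does not support that as the settled meaning; the figure applies to one of two readings. What stands is that both readings are open. In the benefit rule, positive impact is a direction followed by a separate number, and by parallel the negative impact is a direction too.

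**A sensitive trigger can be a sound choice.** The interim aims to pick up adverse effects as well as clear evidence of harm, which would fit two tiers: any adverse average prompts discussion, and 10 points marks harm. The action is cheap and reversible, and the literal rule catches far more trials with a true 10-point excess. This argument stands, so the direction-only rule cannot be called wrong in itself. But if two tiers were meant, the document assigns no action to the higher one.

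**Averaging serves the stated site aim.** The sentence on sites is chiefly about not ending everything because of one site, and averaging with a pause does serve that. The discussion during the pause could also lead to action at one site. A reader might infer that the protocol promises an automatic stop per site and breaks that promise; it makes no such promise. What remains is narrower: if the average does not trigger a pause, no printed step brings a harmful site to anyone's attention.

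**Conclusion.** The pause rule and the harm definition do not match. The 10-point threshold was probably intended, but the printed rule does not contain it. On the literal reading, intake would pause in 43% to 48% of trials with no true effect, against 0% to 16% with a 10-point trigger, assuming 50 to 400 per arm and 10% to 30% prevalence. The claim to allow for site differences has no printed mechanism for detecting or answering harm at one site; the size of the dilution depends on assumed site shares and an assumed 30-point effect.

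The matter is minor to moderate and should be fixed. It would be wrong to conclude that the trial could be terminated on a trivial difference or that its main result is compromised. The consequence is a one-month pause in intake for discussion, and the primary intention-to-treat analysis is unaffected.

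**What to change.** 1. **State the trigger.** Put the size into the first rule: if reoffending prevalence in the treatment group, averaged across sites, is at least 10 percentage points above control, intake pauses for one month. The cost is sensitivity, since this fires in only about 52% to 55% of trials whose true excess is exactly 10 points. If a direction-only pause was intended, say so, accept the false pauses, and state what action the 10-point harm level triggers.

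2. **Support the site claim or drop it.** At the same interim, tabulate the treatment−control difference by site. A large adverse difference should prompt review of that site only, with no automatic pause or stop. The team should set the cut-off, because per-site differences are noisy. As an illustration with a 20-point flag and no true effect, at least one of five sites would be flagged with probability 1 − (1 − P)^5, where P is the chance at one site: 15% to 45% at 20 per arm per site, 1% to 16% at 40, and under 2% at 80. Otherwise delete the statement that the rules allow for site-specific differences.

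The change is one clause and one sentence. Site and allocation are already recorded, so no extra data, sample size or alpha is needed. Some site reviews will prove unnecessary.
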